### Inclusion and exclusion criteria

#### Inclusion criteria

Participants who meet the following criteria will be eligible:Resident residents who have lived in the local area for more than 6 months.Age ≥ 60 years old.Volunteer to participate in the research after fully understanding the project information.

#### Exclusion criteria

The participant may not enter the study if any of the following apply:In the study period, those who did not live in the village due to hospitalizations, traveling, or other reasons did not participate in the study.Aphasia, deafness, blindness, paraplegia, or other physical diseases and/or inability to communicate normally with others.Suffering from major diseases (severe heart, liver, kidney, lung, and metabolic diseases), nervous system diseases that can cause brain dysfunction, or those who have been at the end of their lives.Patients with severe mental disorders, depression, and dementia who have been diagnosed.Loss of daily living abilities.

Participants will receive concise information explanatory statements and an oral description of research details once they agree to participate. An explanation of the study's purpose, the procedure, the use of participant data, requirements of study participants during the 2-year activity, potential benefits and risks, how their information will be kept confidential, and contact information for any questions related to the project will be provided to participants both orally and in writing. Before any investigation is conducted, written consent will be obtained. At any time, participants will be informed that they can withdraw from the study and withdraw their consent. During the study, participants will be asked to maintain daily physical activity and eating habits. There will be no biological specimens collected in the present study.

As a reward for participating in the survey, participants will receive 20 RMB worth of paper towels and detergent. In medicine, the way to ensure participation in medical research through incentives is quite sensitive and controversial [31]. In the present study, although the compensation for the participants seems to be extremely low, the research conforms to the usual ethical standards of human subject research and will not bring additional risks to the subjects. We do not attract and supervise participants through compensation, they all participate in the research voluntarily.

### Interventions

#### Intervention goal

In the 24 months after the intervention, the older people over 60 years old actively participated in chess and cards leisure activities, improving cognitive function and neuropsychiatric symptoms as a result.

### Main intervention components

#### A KAP mode-based approach to intervention

The Knowledge-Attitudes-Belief-Practice (KABP) Model is an important part of the theory of healthy behavior change [32]. The theory holds that acquiring knowledge leads to changes in beliefs and the ultimate goal of establishing healthy behaviors. Positive, correct beliefs and attitudes are built upon knowledge and information. Beliefs and attitudes are the drivers of healthy behavior change. Consequently, this theory plays a significant role in changing unhealthy behaviors and cultivating beneficial behaviors [33]. The purpose of intervention is to improve the knowledge of cognitive impairment, change attitudes, actively participate in chess and cards leisure activities, and then improve cognitive function. Therefore, we adopt strategies to advertise the study, improving the participants' engagement and disseminating the findings.

### Intervention group

Each participant in the intervention group will be given personalized chess and cards leisure activities tools (chess, military chess, gobang, checkers, poker, long cards, etc.) according to their preferences. In addition, we provide education campaigns on the prevention and treatment of cognitive impairment for all residents in the village. Promotion is achieved by publishing relevant popular science content on the village's social platform. Every month, the fixed host convenes the whole village over 60 years old to give a lecture on cognitive impairment prevention. Education focuses on leisure activities and their benefits. Participants are encouraged to plan their leisure time reasonably and take the initiative to participate in various leisure activities, especially social leisure activities such as playing cards and chess. The recommended frequency of chess and cards activities is 5–6 times a week, for at least 1 h. Each village will appoint a responsible person and receive training to motivate their neighbors to actively participate in chess and cards leisure activities. Social support from neighbors and family members will be encouraged through participation in regular activities inside and outside of life. The intervention time was 2 years.

### Control group

Villages assigned to the usual practice control arm were not given any additional activities and were instructed to continue with their normal, everyday activities and hobbies throughout follow-up. Participants in the control group will make the same research measurements at the same time as those in the intervention group.

### Relevant concomitant care permitted or prohibited during the trial

Implementing the intervention will not require alteration to usual care pathways (including the use of any medication) and these will continue for both trial arms. There are no restrictions regarding concomitant care during the trial.

### Outcomes

Uniformly trained researchers will evaluate results at three time points: baseline, 12 months, and 24 months following baseline. During the baseline survey, researchers will fully explain the purpose and content of the study to the participants. If participants are willing to join the study, they will sign a written informed consent. Measurements will only be made after informed consent is given. Cognitive function, depression, anxiety and loneliness, frequency of leisure activities, demographics, and awareness rate of cognitive impairment will be measured. The schedule of enrolment, interventions, and assessments is outlined in Fig. 1.

### Primary outcomes

#### Cognitive function

The Mini-Mental State Examination (MMSE) [34, 35] and Montreal Cognitive Assessment (MoCA) [36] are simple, low cost and noninvasive methods of screening MCI due to Alzheimer’s disease (AD). Numerous studies stated that MMSE and MoCA accuracy in detecting MCI due to AD was inconsistent when selecting different reference standards as the “gold standard. In addition, they selected different cutoff values for positivity. To date, there is still no consensus on which neuropsychological test performs better at detecting MCI due to AD. In addition, international criteria are more suitable as a reference standard for evaluating diagnostic tools' accuracy. Studies have shown that the combined use of MMSE and MoCA scales for cognitive impairment diagnosis is more accurate than MMSE or MoCA scales alone. Therefore, we use MMSE and MoCA together to assess cognitive function. The ability to perform activities of daily living (ADL) is a vital part of the assessment in neurologic patients. An ADL scale was used to evaluate subjects' functional status in real life. It consists of two parts: the Physical Self-Maintenance Scale (PSMS) and Instrumental Activities of Daily Living (IADL).

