### Sample size

PASS 15.0 software calculated the sample size. Power calculation indicated that with a sample size of 4 clusters in each group and 100 observed objects in each cluster, this study would have 88% power to detect the change in cognitive function with a mean of 1, a standard deviation of 2, and a two-tailed significance level of 5%. As a result of the correlation coefficients being set to 0.050 within clusters, and the coefficients of variation being set to 0.650, four clusters in each group, resulting in a total of 800 people to be recruited. The power of RCT over 80% is considered acceptable [41], so the sample size calculated in this study will be eligible.

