### Statistical methods

#### Primary and secondary outcomes

The primary purpose of the analysis was to investigate the effects of multicomponent interventions (targeted promotion campaigns, providing free cards and chess leisure activities tools) on objectively measured cognitive function and neuropsychiatric state, compared with the usual practice at 24-month follow-up.

The primary outcome analysis is powered to detect a significant difference in cognitive function and neuropsychiatric status in the older people over 60 years at the end of a 24-month follow-up period. Linear multilevel models will be used to analyze the cognitive function and other neuropsychiatric indicators as outcome variables. Levels indicate the clustering of residents within villages. We take the randomly divided classification variables as independent variables (the intervention group will be compared with the control group), and age, family history of dementia, baseline value, smoking, drinking, and sleep quality as confounding factors. In these linear multilevel models, village clusters will be included as a random effect to simulate the heterogeneity of residents in villages. The model will use restricted maximum likelihood estimation.

After the survey, the differences in baseline characteristics between participants who completed the whole survey and those who dropped out of the study will be compared. Multiple interpolation and sensitivity analyses of missing data are carried out to evaluate the influence of missing data on the obtained results. The effect size of the protocol will be determined by the subjects who participated in the study and completed follow-up. Secondary outcomes measured at other time points will be analyzed using similar methods. In addition, we will use repeated measurement variance analysis to evaluate the changes in the main outcome indicators of each protocol at each time point. Subgroup analyses are planned for baseline characteristics that might affect the primary outcomes.

The p values of all tests are two-sided and the test level α is 0.05. Estimates will also be reported with a 95% confidence interval.

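### No single primary endpoint is fixed, and the protocol's sections disagree on which outcomes are primary

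*Protocol article*

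**What the plan says.** All places are in the protocol article.

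- **Primary outcomes, Cognitive function.** MMSE and MoCA are introduced, followed by "Therefore, we use MMSE and MoCA together to assess cognitive function". The reason given is that the pair diagnoses cognitive impairment more accurately than either scale alone. The same paragraph continues "An ADL scale was used to evaluate" functional status, with two parts (PSMS and IADL).
- **Primary objective.** Cognitive function at 24 months only.
- **Secondary objectives.** Daily activity function is listed here, as are anxiety, depression and loneliness.
- **Abstract (Methods/design) and Secondary outcomes.** Depression, anxiety and loneliness are secondary.
- **Sample size.** "88% power to detect the change in cognitive function with a mean of 1, a standard deviation of 2, and a two-tailed significance level of" (the level given is 5%). The scale is not named.
- **Statistical methods, Primary and secondary outcomes.** "The primary outcome analysis is powered to detect a significant difference in cognitive function and neuropsychiatric status". The sentence on the primary purpose of the analysis likewise joins cognition and neuropsychiatric state. Scores are analysed with linear multilevel models adjusted for baseline. "The p values of all tests are two-sided and the test level α is 0.05".

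**The concern.** A confirmatory trial needs one statement of what counts as success. Here a reader cannot tell whether the primary test is on MMSE, on MoCA, on a combination, on either or on both. The stated reason for using them together concerns classification of impairment, but the planned analysis compares mean scores and the power is for a mean difference, so the reason does not settle the endpoint.

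Three things are at stake. A split result, such as MMSE significant and MoCA not, has no agreed reading. If either scale may carry the claim, the error rate on the primary question exceeds 5%. And the article tells readers that the primary analysis is powered for neuropsychiatric status, which no calculation in it supports.

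**Working it through.** **1. Passages side by side**

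| Outcome | Treated as primary in | Treated as secondary in | Power calculated? |
|---|---|---|---|
| MMSE, MoCA | Primary outcomes (both, no combination rule) | – (cognition at 12 and 24 months also appears among the secondary objectives) | One unnamed cognitive change |
| ADL (PSMS, IADL) | Primary outcomes (by placement) | Secondary objectives | No |
| Depression, anxiety, loneliness | Statistical methods (primary-purpose and power sentences) | Abstract, Secondary objectives, Secondary outcomes | No |

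The ADL and mood rows each contain a direct conflict. The cognitive row contains an unresolved choice.

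**2. The plan's own power figure**

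Inputs, from Sample size: "4 clusters in each group and 100 observed objects in each cluster", so 400 per arm ("resulting in a total of 800 people to be recruited"); difference 1; SD 2; "correlation coefficients being set to 0.050 within clusters, and the coefficients of variation being set to 0.650". I take the coefficient of variation as that of cluster size.

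- Design effect with equal clusters: 1 + 99 × 0.05 = 5.95.
- Relative-efficiency correction for unequal clusters: L = 5/(5 + 0.95) = 0.840; 1 − 0.65² × 0.840 × 0.160 = 0.943; design effect 5.95/0.943 = 6.31.
- SE = 2 × √(2 × 6.31/400) = 0.355; 1/0.355 = 2.815.
- Two-sided 5%, normal approximation: Φ(2.815 − 1.960) = 80.4%. With t on 6 df: 65.3%.
- One-sided 5%, normal approximation: Φ(2.815 − 1.645) = 87.9%.

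The stated 88% is therefore not reproduced from the two-tailed inputs; under this correction it matches a one-sided 5% test. That is a separate matter. It bears on this point in one way: there is little or no spare power to pay for a second primary scale.

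**3. Error rate if MMSE and MoCA are each tested at two-sided 5% and either suffices**

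Family-wise error = 1 − P(|Z₁| < 1.96 and |Z₂| < 1.96), with bivariate normal test statistics. The documents do not give the correlation, so a range is assumed.

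| Assumed correlation | Chance of at least one false positive |
|---|---|
| 0 (independent) | 1 − 0.95² = 9.75% |
| 0.5 | 9.1% |
| 0.7 | 8.3% |
| 0.8 | 7.8% |

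**4. The same design under explicit rules**

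Power uses the normal approximation and a design effect of 6.31, and assumes that the difference of 1 and SD of 2 apply to each scale used.

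- One named scale at 5%: error 5%, power 80.4%.
- Both scales must be significant: error at most 5%; joint power between 0.804² = 64.6% (independent) and 80.4% (fully correlated).
- Split of 2.5% to each scale: error at most 5%; power per scale 71.7%.

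**The case against.** The strongest reply is that separate testing is inferred. The 0.05 level is a general statement covering all tests, and no sentence says that MMSE or MoCA alone would be a win. Using them together could mean a composite or a both-required rule, and under the latter the error is at most 5%. Scoring and multiplicity rules are also commonly left to an analysis plan, which is not shown. This stands in part: the error rates above are conditional, and the lack of a multiplicity rule is not a fault in itself. It does not remove the point, because an analysis plan cannot make this document's outcome lists agree or supply the calculation that its power sentence implies.

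A second reply is that ADL is a placement slip and that the mood sentence is local wording, overridden by clear labels elsewhere. That is plausible as to intent, and it limits what may be inferred. A reader might count ADL and the three mood scales as further chances to claim improved cognition and quote a much larger error rate. The documents do not support that: ADL is described as measuring function in daily life, and a result on depression, anxiety or loneliness could not be reported as a cognitive benefit. Multiplying up independent tests on the same participants would also overstate the figure.

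A reader might also infer that the trial is badly underpowered because the chosen scale varies more than the SD of 2. No other SD is given, so that cannot be shown. What can be said is that the SD is not attached to any instrument.

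**Conclusion.** The point holds in this form: the article does not fix one primary endpoint, contradicts itself on the status of ADL and of the mood outcomes, and claims power for neuropsychiatric status without a calculation. These faults lie in the text and need no assumption.

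The size is conditional. If either MMSE or MoCA at two-sided 5% counts as success, the error on the primary question is about 7.8% to 9.1% for an assumed correlation of 0.8 to 0.5, with 9.75% under independence. It would be wrong to say that the plan permits a cognitive claim from any one of its scales: the plan does not state that rule. It states no rule, and that is the defect.

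**What to change.** Before any follow-up data are analysed:

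1. Name one cognitive score at 24 months, compared between arms with adjustment for its baseline, as the primary endpoint. Test the other cognitive scale as a key secondary only if the primary is significant. A prespecified composite, or a rule that both scales must be significant, would also resolve the point.
2. State which scale the difference of 1 and SD of 2 refer to, and restate the power if they do not fit the endpoint chosen.
3. List ADL, GDS-30, SAS and the UCLA scale as secondary throughout.
4. In Statistical methods, remove neuropsychiatric status from the power sentence and its equivalent from the primary-purpose sentence.

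The cost is protocol and registry wording. The sponsor gives up a second chance to claim success or, under a both-required rule, accepts joint power below that of a single scale unless the two are fully correlated.

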### Secondary outcomes

#### Depression, anxiety, and loneliness

Depression will be assessed through the Chinese version of the 30-item depression scale for the older people (GDS-30), a popular screening tool for depression that has been in use for more than 30 years [37]. A score of 11 or higher suggests depression. A norm-referenced scale, the Self-Rating Anxiety Scale (SAS), is widely used as a screening tool for anxiety disorders [38, 39]. Loneliness will be assessed using the UCLA Loneliness Scale, which has satisfactory reliability and validity [40].

#### Self-reported chess and cards leisure activities

Participants will be asked to complete a questionnaire on their participation in chess and cards leisure activities. They will also be asked to estimate the frequency and duration of their participation in chess and cards leisure activities. Information on sleep duration and quality, smoking status, drinking status, and exercise status will also be collected through self-reports.

#### Demographic

During their baseline visit, we obtained the following covariates from face-to-face interviews: age, sex, education level, living conditions (living alone or with others), family relations, and monthly income. In addition, participants will report previous illnesses (such as hypertension and diabetes) and a family history of dementia. At each follow-up, participants will be asked if there has been any change in these areas. If yes, it will be revised and the latest follow-up information will be used.

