Although previous studies have provided a great deal of epidemiological reference information about the association of leisure activities with cognitive function, the epidemiological evidence linking specific leisure activities with reducing cognitive decline is not enough to indicate whether these activities have any direct preventive or delaying effects. So far, the evidence from randomized controlled trials supporting the cognitive benefits of leisure activities in the older people through chess and cards is still limited. Most research designs are cross-sectional studies [25] or longitudinal studies [26], and causal inferences cannot be made. Individual randomized controlled trials with a small sample size on cognitive leisure activities are limited to cognitive impairment samples [27, 28]. Therefore, intervention research is needed to prove the causal relationship between chess and cards leisure activities and cognitive function in the population, and to verify whether chess and cards leisure activities are an effective non-drug treatment for the older people. In recent years, social media have been a source of information about cognitive impairment prevention and treatment. This is because massive promotion campaign is also one of the most important aspects of health work. We expect the elderly to voluntarily give up problematic living habits and adopt active lifestyles to delay the decline of cognitive function after being advertised.

Furthermore, there is no single, large-scale, and robust design study to measure the cognitive intervention effect of free chess and cards leisure activities on the older people. To solve this problem, we designed a more convenient and economical cluster randomized controlled trial to avoid contamination and evaluate the real effect of the intervention. We aim to maximize the potential health benefits of chess and cards activities for the older people through intervention. We will not only pay attention to communication campaigns, but also the availability of tools (chess and cards), and improving the activities and atmosphere.

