### Data collection and management

Research assistants blinded to the allocation will be trained in data collection. Participants will be observed and surveyed using questionnaires throughout the study period. The medium-term and long-term effects of the intervention were evaluated by repeated measurements using the same standardized procedures before, 12 months, and 24 months after the intervention.

All collected data will be kept strictly confidential and properly preserved, and all relevant regulations will be observed. Each participant is identified by a unique code instead of a name. All research data can only be obtained by designated research team members before analysis. These data were initially registered on paper questionnaires by investigators and then entered into electronic data through Epidata 3.1 software after the investigation. Electronic data is stored on password-protected computers, and paper questionnaires are stored in locked filing cabinets. When collecting data, the project manager will check all data for omissions or errors and record any problems with the data. Before analyzing the data, the lead researcher (PI) and statistician will review it again. Information collected from the study will be preserved until the project is completed. From the date when the study results are published, they will be preserved for at least 5 years.

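### Using the latest follow-up covariate values lets post-randomisation data into the primary model and the baseline comparisons, and smoking, drinking and sleep quality have no fixed time point

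*Protocol article*

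**What the plan says.** The Demographic section lists covariates obtained at the baseline visit: "age, sex, education level, living conditions (living alone or with others), family relations, and monthly income". It adds that "participants will report previous illnesses (such as hypertension and diabetes) and a family history of dementia". It continues: "At each follow-up, participants will be asked if there has been any change in these areas", and then: "If yes, it will be revised and the latest follow-up information will be used".

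Smoking, drinking and sleep are collected under a different heading, Self-reported chess and cards leisure activities: "Information on sleep duration and quality, smoking status, drinking status, and exercise status will also be collected through self-reports". That section gives no time point and no updating rule.

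Under Statistical methods, the linear multilevel model takes "age, family history of dementia, baseline value, smoking, drinking, and sleep quality as confounding factors". Only the outcome is tied to baseline there. The same section plans subgroup analyses by baseline characteristics and a comparison of baseline characteristics between completers and dropouts.

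Sequence generation places randomisation after each cluster's baseline measurement. Data collection and management describes "repeated measurements using the same standardized procedures before, 12 months, and 24 months after the intervention". The Background section says of the campaign: "We expect the elderly to voluntarily give up problematic living habits and adopt active lifestyles".

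**The concern.** A covariate measured before randomisation cannot be affected by the allocation, so adjusting for it leaves the randomised comparison intact. A covariate measured afterwards has no such protection. If the intervention changes the covariate, or changes how people report it, adjusting for it can remove part of the effect or add bias.

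Here the protocol does more than leave the time point open. It states a rule that prefers the later value, and one item under that rule is in the primary model. Three further model covariates are habits with no stated time point, in a trial that expects its campaign to change habits. At stake are the interpretation of the primary estimate as the effect of the programme, and the validity of two analyses described as using baseline characteristics.

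**Working it through.** **Step 1. What the rule covers and what the model uses.**

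| Item | Under the updating rule | In the primary model |
|---|---|---|
| Age | yes | yes |
| Family history of dementia | yes | yes |
| Sex, education, living conditions, family relations, income, previous illnesses | yes | no (possible subgroup and dropout-comparison variables) |
| Smoking, drinking, sleep quality | no | yes, time point not stated |

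The direct overlap is age and family history. Updating age adds about the same amount for everyone followed to 24 months and does not disturb the treatment comparison. That leaves family history.

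**Step 2. Family history of dementia.** The intervention cannot change a true family history, but the model uses what participants report. Participants are not blinded, and only intervention villages receive monthly lectures on cognitive impairment prevention. If the lectures change the proportion reporting a family history by Δ, and the model coefficient for reported history is β, the treatment estimate shifts by about −β × Δ. The documents give neither β nor Δ, so no size can be stated. If reported history goes with lower scores and reporting rises in the intervention arm, the shift favours the intervention. With the baseline value, randomisation gives Δ an expected value of zero.

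**Step 3. Subgroup and dropout comparisons.** Under the rule, someone who completes carries values updated up to 24 months, and someone lost before the first follow-up carries the original ones. The comparison then mixes dates: read literally, even age would differ by up to 2 years for that reason alone. For subgroups, items such as family relations would no longer be pre-randomisation, and the intervention text encourages family support.

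**Step 4. Smoking, drinking and sleep quality (conditional).** Let f be the share of the effect that runs through these habits. If follow-up values are adjusted for, and nothing unmeasured drives both habit and cognition, the estimate is

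estimate = (1 − f) × true effect.

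The documents do not give f, so it is assumed. With a true effect of 1 point (the Sample size section), f = 0 gives 1.00, 0.10 gives 0.90, 0.20 gives 0.80 and 0.30 gives 0.70.

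A simulation checked the mechanism: 8 clusters of 100, SD about 2, ICC 0.05, one covariate with baseline-to-follow-up correlation 0.6, 400 runs per setting, least-squares point estimates.

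| Mediated part | Adjusting for baseline value | Adjusting for follow-up value | Difference |
|---|---|---|---|
| 0.00 | 1.01 | 1.01 | 0.00 |
| 0.10 | 1.02 | 0.92 | 0.10 |
| 0.20 | 0.97 | 0.78 | 0.20 (unrounded 0.975 − 0.776) |

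The departures from 1 in the baseline column are Monte Carlo noise. The loss equals the mediated part, and it is zero when there is none.

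**Step 5. What that would mean for power.** The plan's own figure comes first. Inputs from the Sample size section are 4 clusters of 100 per arm, difference 1, SD 2, ICC 0.05, coefficient of variation 0.65 and two-sided 5%.

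- Design effect with equal clusters: 1 + 99 × 0.05 = 5.95.
- Relative efficiency for unequal clusters: λ = 5/5.95 = 0.840, and 1 − 0.65² × 0.840 × 0.160 = 0.943. The design effect becomes 5.95/0.943 = 6.31.
- SE = 2 × √(2 × 6.31/400) = 0.355.
- Power = Φ(1/0.355 − 1.96) = 80.4%.

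The stated 88% is not reproduced two-sided; a one-sided 5% test gives 87.9%. That is a separate matter, and this point does not rest on it. From 80.4%, the same formula gives 76.3% at f = 0.05, 71.7% at 0.10, 61.5% at 0.20 and 50.4% at 0.30. With a t reference on 6 degrees of freedom the start is 65.3%, and f = 0.30 gives 38.2%.

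**The case against.** A reader might infer that the updating rule overwrites smoking, drinking and sleep quality, and hence that part of the effect is adjusted away. The documents do not support this. The rule refers to the items in its own paragraph, and these three are collected elsewhere without such a rule. Repeat collection is plausible from the repeated-measurement design but is not stated for them, and collecting a value again does not put it in the model. The loss also requires the campaign to change these habits. The Background section speaks of living habits in general, while the intervention text centres on leisure activities and has no component aimed at smoking, alcohol or sleep. All of this stands, and it makes that part of the point conditional.

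It can also be said that the time point of a covariate is usually left to the analysis plan. For smoking, drinking and sleep quality alone, that would carry weight. It does not answer the rule in the Demographic section, which is stated and says which value to use.

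Differential reporting of family history is a possibility without a figure behind it. That is fair, but the baseline value avoids the question at no cost. Asking again about living conditions or illnesses is ordinary data collection and is not criticised here; the fault lies in replacing the earlier value.

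Finally, a reader might take the absence of sex and education from the model as a bias. It is not one in a randomised comparison, and this point does not depend on it.

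**Conclusion.** The point holds in a limited form. The stated rule admits a post-randomisation value of reported family history of dementia into the primary model. It also conflicts with the plan to use baseline characteristics for subgroups and for comparing completers with dropouts. Both follow from the text as written; the size of any resulting bias cannot be derived from it.

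For smoking, drinking and sleep quality the fault is an unfixed time point. Attenuation follows only if follow-up values are used and the intervention changes these habits. Under an assumed mediated share of 0% to 30%, a true 1-point effect would be estimated at 1.0 to 0.7, and recomputed two-sided power (normal approximation) would run from 80.4% down to 50.4%. At 0% nothing is lost, and the documents do not indicate where in that range the trial lies.

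**What to change.** Replace the updating sentence in the Demographic section with a rule that keeps the baseline value unchanged and stores each follow-up answer as a separate, dated variable.

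Add to Statistical methods that every covariate used for adjustment, subgroups or the completer-versus-dropout comparison takes its pre-randomisation baseline value. Name age, family history of dementia, smoking, drinking, sleep quality and the other items of the Demographic section. Follow-up values may then be used only in analyses labelled exploratory, for example of mediation.

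The cost is two sentences, the matching registry update and extra columns in the database. No new data are needed. Answers are first recorded on paper and the questionnaires are kept, so a baseline value already overwritten in the electronic file could be restored. The change should be made before any outcome data are analysed.
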